### Public Involvement

As mentioned in the intervention details, members of the public will be used to disseminate promotional messages through social media, using decals, active participation in groups and community events. During the pilot phase, we also incorporated their feedback for improving intervention delivery techniques and platforms prior to the trial.

### Eligibility Criteria

We randomly selected 5 town panchayats from each district. Researchers visited several wards with local Swasti officials to ensure they reflected the generalized peri-urban setting. To identify potential study wards within these town panchayats, we met local executive officers to assess ward maps. We used the following exclusion criteria: commercialized wards with few residential households, urbanized wards with known high or complete coverage of improved toilet access according to town panchayat official records, and wards which bordered two or more adjoining wards (to reduce spillover).

Our sampling frame excluded town panchayats where we piloted our interventions (n=3) or those where we did not receive permission to proceed due to political concerns (n=1).

The unit of randomization for this CRT was the ward. The demarcation of the ward was derived from the 2011 census conducted by the Ministry of Home Affairs of the Government of India [34]. Trained field teams generated ward maps to delineate the ward boundaries, confirmed it with residents, and ensured a buffer zone. We also engaged ward-level stakeholders to assist in the mapping process and gain access to communities. From the ward maps, we identified the adjoining wards, which share the borders and excluded 1 from the list of potential wards to ensure we reduced the possibility of spillover between clusters. Of the total of 153 wards considered in 10 town panchayats, we found 79 eligible wards based on our criteria. We selected a random sample of 76 wards to include in our study. These wards are more representative of residential peri-urban wards in Tamil Nadu. As the treatment arm was randomly selected, we do not expect to find systematic differences between the treatment and control arms. Following this exercise, a minimum of 1 km distance was ensured between the residential units in each cluster.

All ward residents from intervention clusters are eligible to participate in the intervention activities. For data collection, field workers surveyed randomly selected household members who were 18 years or above, planned to reside in that household continuously for the next year, and were willing and able to participate.

### Selection and Assignment of Interventions

Following the baseline data collection, a coinvestigator [name] randomly assigned the wards to counterfactual and intervention arms in a 1:1 ratio, using a computer-generated randomization sequence. The randomization was geographically pair-matched within each town panchayat (Multimedia Appendix 1). Balancing the study arms across geography will allow us to adjust for spatially clustered features or events that may be associated with our outcome. Given the nature of the intervention, the study investigators and the participants will not be masked to the intervention assignment. The data collection team will be masked to the treatment assignment.

### Recruitment

Trained enumerators conducted a listing exercise to generate a sampling frame of eligible individuals within each ward. Enumerators approached the household and asked the selected individuals if they would consent to participate in the study. If the selected individual was absent or unavailable, up to three repeat visits were made to enroll them. If unsuccessful, the enumerators approached the next randomly selected individual from that cluster. Following randomization, households in intervention wards were enrolled following an oral consent process.

The individuals enrolled in qualitative studies will be purposively selected from intervention wards to address relevant research questions. Those sampled from the counterfactual wards will allow us to investigate spillover of the Nam Nalavazhvu intervention.

### Sample Size

This study is powered to detect differences in the prevalence of exclusive toilet use between study arms. Measuring exclusive use is problematic due to recall and desirability bias. As a result, during our formative research phase, we asked individuals about their defecation place the last time they needed to defecate during 2 rounds of data collection conducted 8 months apart. We incorporated the correlation between these 2 measures in our sample size calculation. We powered our study at 80% based on the prevalence of reported toilet use during last defecation in peri-urban Tamil Nadu (estimated at 64.4% in 2018) and assumed a 10-percentage-point improvement as the minimum important effect [26]. To detect such a minimal effect in exclusive toilet use (given an observed intracluster correlation of 11% and correlation of last use with the one measured in the fall of 2017 of 47.5%) [26], we estimated a requirement of 76 clusters (38 clusters per arm). We require 30 individuals per cluster. Assuming 10% loss to follow-up, we will engage 34 individuals per cluster for a total of 2280 individuals. As we will collect household level toilet usage data, we will have data for more individuals beyond the actual number of respondents.

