### Specific Aims

The primary research aim of this study is to evaluate the impact of the Nam Nalavazhvu intervention on behavioral and health outcomes. The aim specifically focuses on the following: exclusive toilet usage, defined as reported use of a toilet every time for defecation among individuals aged 5 years and older (primary outcome).

Secondary aims include assessing the impact of the intervention on the following: access to improved toilets (individual or shared) for households without a toilet; maintenance of sanitation facilities for sustained use; empirical expectations, normative expectations, and other behavioral antecedents; mental well-being of respondents; and diarrheal outcomes in all household members and respiratory health in children under 5 years.

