#### Community Mobilization and Commitment Events

Participants will include influential political and community leaders to applaud exclusive toilet users and promote improved sanitation practices. Messages will highlight the change happening in their communities and the benefits of using a toilet for families, and facilitate a public commitment to exclusive toilet use. These messages will reinforce those heard by residents through other group and household activities.

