#### Visual Signals of Improved Practices

Improved behaviors of neighbors will be signaled using bright decals or stickers, placed in public view on the household wall. These aim to serve as a goal and a source of pride for the households who receive and display them.

During the trial of improved practices, we incorporated feedback from community members and pilot intervention recipients to ensure the feasibility, appropriateness, and acceptability of the content, and the delivery mechanism of the Nam Nalavazhvu intervention activities. Notably, we confirmed that signaling toilet ownership and use through stickers, household visits, group meetings, and testimonials were acceptable and perceived as encouraging and aspirational. We ensured that all content used positive framing and included engagements with community stakeholders to collaboratively host group and community events. We also assessed whether incentives were necessary for the influencers, and found they preferred nonmonetary compensation or incentives. We plan to recognize them at community events for their work, present them with a volunteer experience certificate, and invite them to group sessions held as a part of the intervention activities.

The implementation team is hired and managed by Swasti. Investigators at the Center for Social Norms and Behavioral Dynamics (CSNBD) at the University of Pennsylvania will provide training, technical input, and oversight to the implementation process. The main delivery agent will be ward outreach workers who are residents of the ward with a minimum of 12 years of formal education. Field supervisors will help organize and facilitate group and ward-level activities. In addition, the study will include influential members from the community to disseminate promotional and motivational messages to their social networks.

Participation in these activities will be voluntary. The audio announcements and visual cues or paintings in public spaces will be apparent during the intervention. Ward outreach workers will consider any requests to adjust the recipient’s level engagement in the activities to ensure the consent and comfort of participants.

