#### Primary Outcome

The primary outcome will be the proportion of households where all members (18 years or older) exclusively use a toilet every time they defecate. We will combine responses to several self-reported toilet use behaviors to determine exclusive toilet use in the previous 2 days. We will also observe toilets to check for signs of use (Multimedia Appendix 2).

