#### Secondary Outcomes

There will be 5 secondary outcomes: (1) presence and access to improved toilets will be assessed using standard questions, while spot observations of toilets will be used to assess maintenance, functionality, and recent use; (2) mental well-being will be measured using The 5-item World Health Organization Well-Being Index (WHO-5); (3) diarrheal disease for all household members will be measured using the WHO definition of three or more loose stools in a 24-hour period, with or without the presence of blood; (4) respiratory illness for children under 5 years will be measured using reported cough and/or difficulty breathing or shortness of breath according to the WHO’s Integrated Management of Childhood illness; and (5) intermediate behavioral antecedents such as empirical expectations (ie, what other people do), normative expectations (ie, what other people think one should do) of prevalence of toilet ownership, exclusive use, and maintenance will be measured using tested indicators (see Multimedia Appendix 2)

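### The primary outcome rests on self-reports that the article calls desirability-prone, the intervention publicly promotes that behaviour in one arm only, and the toilet observations have no stated role as a check

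*Protocol article*

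**What the plan says.** All references are to the protocol article.

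- **The warning.** Sample Size states: "Measuring exclusive use is problematic due to recall and desirability bias". The formative surveys therefore asked where the respondent last defecated, and the trial was sized on that item (64.4% in 2018).
- **The outcome.** Specific Aims gives "exclusive toilet usage, defined as reported use of a toilet every time for defecation among individuals aged 5 years and older (primary outcome"). Primary Outcome makes it a household measure covering all adults and says: "We will combine responses to several self-reported toilet use behaviors to determine exclusive toilet use in the previous 2 days".
- **Observation.** The next sentence of Primary Outcome adds: "We will also observe toilets to check for signs of use (Multimedia Appendix 2"). Secondary Outcomes, under item 1, says "spot observations of toilets will be used to assess maintenance, functionality, and recent use". The text does not say how either observation bears on the primary classification.
- **What only intervention wards receive.** Community Mobilization and Commitment Events: "Participants will include influential political and community leaders to applaud exclusive toilet users and promote improved sanitation practices". The same events are to "facilitate a public commitment to exclusive toilet use". Visual Signals of Improved Practices: "Improved behaviors of neighbors will be signaled using bright decals or stickers, placed in public view on the household wall". Under Study Design, the other wards get no active study intervention.
- **Masking.** Participants know their assignment (Selection and Assignment of Interventions). Enumerators are masked but may see intervention products at follow-up (Data Collection).
- **Analysis and limitations.** Statistical Analyses compares outcomes between arms and is silent on differential reporting. The limitations paragraph of the Discussion does not mention it.

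**The concern.** Over-reporting that is equal in both arms mostly dilutes a difference. Over-reporting that is greater in one arm creates one. Here the intervention raises the social value of one particular answer, and that answer is the primary outcome. A resident who has pledged in public, or whose wall carries a sticker, has a reason to report exclusive use that a control resident lacks.

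The motive sits with the respondent, so a perfectly masked enumerator would record the same answer. A 2-day window helps memory but not candour. Randomisation does not protect against a bias that arises after allocation, and more wards would only estimate the biased difference more precisely. A positive primary result could therefore be partly a change in what people say.

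**Working it through.** **1. The plan's own figure.** Inputs from Sample Size: 64.4% against 74.4%, power 80%, intracluster correlation 0.11, 30 per ward, correlation 0.475 with the earlier measure. Two-sided 5% is assumed because no level is stated.

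- Unclustered n per arm: 333 without and 352 with continuity correction.
- Design effect: 1 + 29 × 0.11 = 4.19.
- Gain from the earlier measure: 1 − 0.475² = 0.774.
- Wards per arm: 352 × 4.19 × 0.774 / 30 = 38.07, or 76.1 in all (36.0 per arm without the correction).

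The stated 76 is reproduced. The sample size is not at fault here.

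**2. How reporting turns into an apparent effect.** Let p be the proportion who would report the outcome under control conditions. Let o be the share of the rest who report it in the intervention arm with no change in behaviour. With zero true effect, the expected difference is o × (1 − p).

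**3. Over-claiming needed for the target effect.** Assume p = 0.644, so 1 − p = 0.356. Then o = 0.10 / 0.356 = 0.281, about 28%.

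**4. Over-claiming needed for a just-significant difference.** With 38 × 30 = 1,140 per arm and prevalence 0.669 (midway between 64.4% and 69.4%):

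- SE = √(2 × 0.669 × 0.331 × 4.19 / 1,140) = 0.0403.
- Without the correlation gain: 1.96 × 0.0403 = 0.079, and 0.079 / 0.356 = 22%.
- With it: 0.079 × √0.774 = 0.070, and 0.070 / 0.356 = 20%.

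Taking prevalence as 0.694 instead gives 22% and 19%.

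**5. Chance of a significant result favouring the intervention when the true effect is zero** (nominal 2.5%; the range is without and with the correlation gain):

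| Extra over-claiming | Spurious difference | Chance |
|---|---|---|
| 5% | 1.8 points | 6-7% |
| 10% | 3.6 points | 14-17% |
| 15% | 5.3 points | 26-33% |
| 20% | 7.1 points | 43-53% |
| 28% | 10 points | 72-82% |

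**6. Dependence on the base rate.** The 64.4% refers to individuals' last defecation, whereas Primary Outcome counts households in which every adult is an exclusive user. No base rate is given for that. It could be lower, because the criterion is stricter, or higher, because 64.4% dates from 2018 and both districts were declared open defecation-free in October 2019. For a 10-point difference, o = 0.10 / (1 − p): 20% if p = 0.50, 28% if p = 0.644, 50% if p = 0.80.

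**The case against.** **The toilets are observed.** This is the strongest point, and part of it stands. Observation takes place in both arms and does not depend on what the respondent says. A reader might infer that a positive result could not be told apart from a change in talk; the documents do not support that, because a comparator is being collected. What remains is that the text gives it no role in the primary outcome and lists spot observation under a secondary one. Signs of use also cannot show that every adult used the toilet every time. Multimedia Appendix 2 may contain a combination rule, or may already include last-use among the reported items, so the question to the sponsor is what that rule is.

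**The stickers may not reward a mere claim.** This stands. A reader might infer that an unverified statement earns public recognition. The article says improved behaviour is signalled and users are applauded; it does not say how, or whether, use is checked first. The public commitment is explicit and is enough for the concern.

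**Last-use is no cure.** This stands too. It is also self-reported, and a pledged respondent has much the same motive to answer favourably. The article blames recall and desirability together and never says last-use resolves the second. Agreement between the two items would not rule out over-claiming.

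**The figures lack a documented basis.** Agreed: no over-claim rate appears anywhere, and the base is borrowed from a different measure. They show sensitivity, not expected bias.

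**Other safeguards, and the analysis plan.** Masked enumerators, short recall, routine monitoring kept away from survey participants, and qualitative triangulation all help, and Specific Aims already says reported use. None is tied to the primary contrast. A sensitivity analysis may properly sit in an analysis plan, so its absence here is not the point. The point is that the article names a bias, fixes an outcome exposed to it, and leaves the available check without a stated role.

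**Conclusion.** The concern holds as a foreseeable risk of bias in favour of the intervention, not as a demonstrated one. It rests on four stated facts: the article's own warning, a self-reported primary outcome, public promotion of that behaviour in one arm only, and unmasked respondents. If 64.4% is taken as the base, about 28% extra over-claiming would mimic the full 10-point effect, about 20-22% would reach significance, and 10% would raise the favourable false-positive chance from 2.5% to roughly 14-17%. These sizes assume a zero true effect, 38 wards of 30 per arm, two-sided 5%, and a base rate that belongs to individual last-use rather than the household outcome. The text does not show that reports will be inflated, that recognition is given unchecked, or that the trial will be uninterpretable. It does show that the conclusion needs a stated limit and that the means of setting one are already being collected. The change should be made before endline data are analysed.

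**What to change.** 1. **Primary Outcome and Statistical Analyses:** prespecify the observed signs of use, already collected in both arms, as the main corroborating outcome. Compare them between arms in the same model. Report by arm the share of households reporting exclusive use whose toilet is absent or shows no signs of use. State whether Multimedia Appendix 2 already gives observation a part in the primary classification.
2. **Supporting outcome:** also report the respondent's place of last defecation, the measure on which the trial was sized, noting that it too is self-reported and that agreement is not proof.
3. **Tipping point:** beside the primary estimate, report the extra over-claim rate among non-exclusive households in the intervention arm that would reduce it to zero. This is the estimated difference divided by one minus the trial's own control-arm proportion.
4. **Wording:** state the conclusion as 'reported exclusive use' unless the observed evidence agrees in direction, and add arm-specific reporting to the limitations.

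Cost: at most one survey item, a little more analysis, and a more cautious conclusion if the measures disagree. Even agreement would leave a residual limit, since observation cannot establish use by every adult on every occasion.

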### Study Outcomes and Measures

We will evaluate these outcomes at baseline and at endline in both the intervention and counterfactual clusters 1 year after the intervention implementation using verbal surveys. We will characterize sanitation facilities using standardized categorizations through direct observations.

#### Primary Outcome

The primary outcome will be the proportion of households where all members (18 years or older) exclusively use a toilet every time they defecate. We will combine responses to several self-reported toilet use behaviors to determine exclusive toilet use in the previous 2 days. We will also observe toilets to check for signs of use (Multimedia Appendix 2).

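### The primary outcome is defined in two incompatible ways (individuals aged 5 and over, or households in which every adult complies), and the sample size rests on a third measure

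*Protocol article*

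**What the plan says.** Two current sections of the protocol article each name the primary outcome.

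- Specific Aims: "exclusive toilet usage, defined as reported use of a toilet every time for defecation among individuals aged 5 years and older (primary outcome".
- Under the Primary Outcome heading: "The primary outcome will be the proportion of households where all members (18 years or older) exclusively use a toilet every time they defecate". The next sentence adds a recall window: "We will combine responses to several self-reported toilet use behaviors to determine exclusive toilet use in the previous 2 days".

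Sample Size uses neither. Its control rate is the "prevalence of reported toilet use during last defecation in peri-urban Tamil Nadu (estimated at 64.4% in 2018", it "assumed a 10-percentage-point improvement as the minimum important effect", and it counts 30 individuals in each of 76 wards.

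Sample Size also says that toilet use will be recorded for the household, so data will exist for more people than the respondents. Secondary Outcomes lists five outcomes, and neither version of exclusive use is among them. Statistical Analyses specifies log-binomial regression with generalized estimating equations clustered on ward and no multiplicity adjustment. It does not say whether one record is a person or a household.

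**The concern.** The two statements define different quantities. One is a prevalence among people that includes children from age 5. The other is a prevalence among households that ignores everyone under 18 and scores a household as a failure if a single adult does not comply. Control level, absolute effect and prevalence ratio all depend on which is used.

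Both versions appear computable from the household data to be collected, and no rule says which one is confirmatory. Investigators are not masked to allocation and P values will not be adjusted. If the question is settled only after endline, the more favourable version could become the primary result. The 80% power cannot settle it either, because it was worked out for a third quantity.

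**Working it through.** **1. The definitions side by side**

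| | Specific Aims | Primary Outcome | Sample Size |
|---|---|---|---|
| Unit | individual | household | individual |
| Age | 5 and over | 18 and over | not stated |
| Success | every-time use by the person | every-time use by all adults | toilet used at last defecation |
| Recall window | not stated | previous 2 days | last defecation |

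**2. Which measure the stated sample size belongs to**

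Inputs from Sample Size: 64.4% against 74.4%; power ("We powered our study at 80" percent); 30 individuals per cluster; and "given an observed intracluster correlation of 11% and correlation of last use with the one measured in the fall of 2017 of 47.5" percent. Assumed, because not stated: two-sided 5% test, and baseline adjustment through the factor 1 − r².

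- Two-proportion sample size without clustering: 333 per arm.
- Design effect: 1 + (30 − 1) × 0.11 = 4.19.
- Baseline factor: 1 − 0.475² = 0.774.
- Required: 333 × 4.19 × 0.774 ≈ 1,080 individuals per arm; 1,080 / 30 = 36.0 clusters. The unrounded value is 36.02, so 37, and one extra cluster per arm gives 38.
- With a continuity correction (352 per arm) the result is 38.07 clusters. Without the baseline factor it is 46.5, which does not match.

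The stated 38 clusters per arm is thus recovered, up to the final rounding step, from individual-level last-defecation inputs.

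**3. How far apart the person and household versions are**

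The documents give neither the number of adults per household nor the within-household correlation ρ. Assumed: 1 to 6 adults in 10%, 35%, 25%, 20%, 7% and 3% of households; ρ from 0.5 to 0.9; the same individual rate p at every household size; and 64.4% standing in for the every-time rate.

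Beta-binomial model: P(all k adults comply) = product over j = 0, …, k − 1 of (a + j)/(a + b + j), with a = p(1 − ρ)/ρ and b = (1 − p)(1 − ρ)/ρ. For two adults this is p[p + ρ(1 − p)]. At ρ = 0.6 that gives 0.644 × (0.644 + 0.6 × 0.356) = 55.2% and 0.744 × (0.744 + 0.6 × 0.256) = 66.8%.

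Averaged over the assumed household sizes:

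| ρ | control | intervention | difference (points) |
|---|---|---|---|
| 0.5 | 49.0% | 61.3% | 12.3 |
| 0.6 | 52.2% | 64.1% | 11.9 |
| 0.7 | 55.3% | 66.7% | 11.4 |
| 0.8 | 58.4% | 69.3% | 11.0 |
| 0.9 | 61.4% | 71.9% | 10.5 |
| per person | 64.4% | 74.4% | 10.0 |

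**4. Power under the household version**

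Assumed: one household per respondent, with ICC 0.11 and r = 0.475 carried over. Under the same individual-level shift, power with 38 clusters of 30 per arm does not fall below the 82% of the individual outcome. If a 10-point effect is kept on a household rate of 40% to 50%, power is about 76%, and about 42 clusters per arm would be needed before any extra cluster.

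**5. Type I error if either version may count**

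Two independent tests at 5% give 1 − 0.95² = 9.75%. The two outcomes come from the same households and are positively correlated. In the model above (adults only) the correlation is about 0.79 to 0.89, which gives roughly 7% to 8%. Children aged 5 to 17 could lower the correlation somewhat.

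**The case against.** **The dedicated outcome section probably governs.** It gives the recall window and points to an appendix of outcome measures that is not shown, whereas Specific Aims is a short statement of purpose. A reader might infer from the conflict that the trial has no primary result at all, or that the investigators mean to choose between two. The text supports neither reading: one section is the natural default, and nothing plans a choice after endline. The contradiction remains, because both sentences carry the primary label and no appendix could make both true.

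**The gap in level is not a gap in effect.** A reader might set the 3 to 15 points between the individual and household control rates against the 10-point target. That compares a level with a difference. On the same assumptions the effects are 10.5 to 12.3 points against 10. Nor does the household version necessarily lose power.

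**Sampling.** Recruitment says: "Trained enumerators conducted a listing exercise to generate a sampling frame of eligible individuals within each ward". A reader might infer that large households are over-represented and that each household needs a weight of 1/(listed adults). The article does not describe selection within households. In the model above, size-biased sampling moves the effect by only 0.1 to 0.3 points. With 34 respondents from every ward whatever its size, such a weight alone would not recover the overall proportion of households. This part does not stand.

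**Conclusion.** The contradiction is established from the text alone, without any modelling. It is not a detail left to a fuller document, because the article states the primary outcome twice and differently, and powers the trial on a third measure. Until it is resolved the confirmatory estimand is not fixed, so it should be corrected before endline data are seen by arm.

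The size is moderate and rests on assumed household sizes and correlations: control about 49% to 61% against 64.4%, and an effect of about 10.5 to 12.3 points against 10. The type I error from a free choice would exceed 5%. The 9.75% figure is a bound under independence, which two such closely related outcomes would not reach.

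**What to change.** Before endline data are seen by arm:

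1. State one unit, one age range and one recall window for the primary outcome, identically in Specific Aims and Primary Outcome. The Primary Outcome section is the natural default, but the choice is the investigators'.
2. Name the other version as a secondary outcome in Secondary Outcomes, and update the count of five.
3. State in Statistical Analyses whether the primary analysis record is a person or a household.
4. Say in Sample Size that the 80% power refers to individual use at last defecation, or restate power for the chosen outcome with its own control rate, ICC and baseline correlation.

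The cost is a wording amendment, a registry update if needed, and one recalculated power statement. No new data and no household-size weighting are required.
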